### Aims, Objectives, and Hypotheses of TANDem-2

#### Overview

The study aims and hypotheses are outlined below. Specific objectives linked to the aims are shown in Textbox 1.

Aims and objectives of the TANDem-2 project.
**Aim 1: Examine longitudinal trajectories of tuberous sclerosis complex (TSC)–associated neuropsychiatric disorders (TAND) severity and predictors of differential trajectories**
1.1: Adapt the TAND Toolkit app for longitudinal data collection.1.2: Collect the self-report quantified TAND checklist and other relevant questionnaires longitudinally from 500 participants at 5 time points over 12 months.1.3: Use data collected in 1.2 to identify longitudinal trajectories of TAND severity and potential predictors of differential trajectories.
**Aim 2: Examine caregiver well-being as a possible mediator of TAND severity and severity trajectories**
2.1: Using data collected in aim 1, examine the relationship between caregiver well-being, TAND severity, and its trajectories.
**Aim 3: Adapt and evaluate the feasibility, acceptability, and potential efficacy of a brief caregiver well-being intervention**
3.1: Use participatory methods (experiential and adaptation workshops) to adapt the “Well-Beans for Caregivers” intervention materials specifically for family caregivers of individuals with TSC of any age, as well as the methods for online delivery.3.2: Evaluate the feasibility, acceptability, and perform limited efficacy testing of the adapted “Well-Beans for Caregivers” intervention in a small pilot trial.

#### Aim 1: Examine the Longitudinal Trajectories of TAND Severity and Their Predictors

We hypothesize that longitudinal analysis of TAND severity data will identify at least 3 differential trajectories (“stable,” “worsening,” “improving”), and that trajectory membership will have differential predictors. To test this hypothesis, we will use an accelerated longitudinal design to collect longitudinal data from 500 families across 5 time points with 3-month intervals over a 12-month period.

#### Aim 2: Examine Caregiver Well-Being Factors as Mediators of TAND Severity and TAND Severity Trajectories

We hypothesize that cross-sectional mediation modeling will identify specific caregiver well-being factors that mediate or moderate TAND severity of TSC family members, and that sequential causal mediation analysis of those factors will identify predictors of longitudinal TAND severity outcomes over time. These specific caregiver well-being factors could include caregiver psychosocial burden, caregiving burden, levels of resilience, depression or anxiety, or overall well-being. To test this hypothesis, the caregiver dataset generated for aim 1 will be used. First, SEM will be used for mediation modeling of baseline data (T_0_). Next, trajectory membership and their predictors identified in aim 1 will be combined with the caregiver mediator factor confirmed through SEM to perform sequential causal mediation analysis.

#### Aim 3: Adapt and Perform a Pilot Feasibility and Potential Efficacy-Testing of an Innovative Brief Caregiver Well-Being Intervention

We hypothesize that an innovative, brief caregiver well-being intervention developed for caregivers of children with developmental disabilities can be adapted as a caregiver well-being intervention in TSC, that it can be delivered feasibly in an online modality, and that we will observe signals of change in key caregiver well-being factors identified in the longitudinal trajectory (aim 1) and mediation analyses (aim 2). To test these hypotheses, we will use participatory methods with the TAND consortium to adapt the 3-session “Well-Beans for Caregivers” program for the TSC caregiver community. After adaptation, we will deliver the 3-session intervention online to 3 groups of 10 caregivers each using a quasi-experimental pre-post follow-up design including measures of the key caregiver well-being factors examined in the mediation modeling and additional measures specific to the intervention. As mandated by our funding agency, only a pilot trial will be conducted.

A visual summary of the TANDem-2 project is provided in Figure 3.

**Figure 3 figure3:**
[figure not shown]
A visual summary of the TANDem-2 project. TAND: tuberous sclerosis complex–associated neuropsychiatric disorders; TSC: tuberous sclerosis complex.

## Methods

### Study Participants Aims 1 and 2

#### Inclusion Criteria

A total of 500 adult participants (>18 years of age) will be recruited. Inclusion criteria are (1) adult individuals with TSC of any age, sex, genotype, and an intellectual level that will allow them to participate in the study; (2) adult caregivers (>18 years of age) of individuals with TSC (of any age, sex, genotype, and intellectual level); (3) willingness to provide informed consent; (4) willingness and ability to complete data collection at 5 time points over a period of 12 months using the TAND Toolkit app; (5) access to a smartphone or other digital device (eg, tablet, laptop, or desktop computer) and mobile data or internet access to complete data collection using the app; (6) sufficient knowledge of technology to be able to access the web-based smartphone app on their digital devices; and (7) sufficient understanding of English to be able to understand the study information and consent documents, and to complete the English questionnaires included in the study.

#### Recruitment

Study participants will be recruited through TSC International (TSCi), the umbrella organization for all international TSC nonprofit organizations. TSCi represents a total of 38 individual organizations across the globe, including the TSC Alliance, based in the United States. The TSC Alliance has a global reach for research recruitment, including the Natural History Database, which includes over 2700 participants at the time of writing [40,41]. Family representatives within the TAND consortium are active advocates within their country-specific patient organizations, who will assist with recruitment efforts. Within the TAND consortium, we will cocreate a study flyer with a description of the study and an invitation to participate. The flyer and invitation to participate will be sent electronically by the TSC Alliance and other TSCi partner organizations to TSC families in their networks via their websites, mailing lists, and other organizational communication strategies. Word-of-mouth and snowball sampling may also play a part once recruitment begins.

#### Enrollment

Individuals who wish to participate in aims 1 and 2 of the TANDem-2 research project will be required to register online and use the TAND Toolkit app for data collection. Informed consent will be captured electronically. To optimize potential participant understanding of study participation requirements, and in line with current recommendations regarding electronic consent processes [69-72], we have incorporated various elements in the recruitment and enrollment process. Interested participants will be able to click on a link or scan the QR code on the flyer to access further information about the study on a dedicated web page on the TAND consortium website [73]. This study’s web page will contain detailed information about the study in various formats: a short video about the TANDem-2 project, a visual summary of the steps involved in data collection, a PDF document of the approved study information, and consent form, as well as the privacy policy and terms of use for the TAND Toolkit app, a set of accessible frequently asked questions, and an email address where any study related questions can be directed to the research team. If interested individuals would like to join this part of the study, they can click on the button at the bottom of the project information web page to proceed to the TAND Toolkit app registration web page. The first step will be to read and complete the digital study information and consent form, as well as the app privacy policy and terms of use. The participant will then proceed to complete the registration process and create an app user account. The participant (app user) will then receive an email to verify their account registration, and thereafter will receive access to the TAND Toolkit app. These registration steps are in line with current recommendations to enhance data integrity while using an exclusively digital data collection method [74-79].

#### Retention

In light of the risk of attrition in longitudinal research, retention will be facilitated by a range of retention strategies shown to be effective in large-scale longitudinal studies [80]. These will include inviting more than the target number of participants to enroll (up to 600), incentivization through invitations to study webinars, and study updates and activities linked to TSC Alliance and TSCi events. Participants will not be compensated for participation, another key feature for enhancing data integrity in digital research [78]. Further technical retention strategies built into the TAND Toolkit app are described in the measures and data collection methods for aims 1 and 2 under the “Measures and Data Collection” section.

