**Results:**

This study was funded from July 2024 (HT94252410790 and HT94252410791), and ethics approvals were obtained from the University of Cape Town (July 2024), Vrije Universiteit Brussel (November 2024), and the Department of Defense Office of Human Research Oversight (December 2024). The TAND Toolkit app was adapted for longitudinal data collection (aims 1 and 2). Recruitment started in December 2025 and will continue until 500 participants are enrolled (anticipated December 2026). Primary outputs are expected by July 2028. For aim 3, experiential and adaptation workshops were completed in June 2025, the pilot intervention was delivered in November 2025, and data collection will continue till May 2026. Outputs are expected by December 2026.

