### Data Analysis

#### Statistical Analysis Plan (Aim 1)

TAND severity will be quantified using the CSS_mean_ for each cluster and the TTSS_mean_/TTSS_max_ for overall TAND severity. These will be used to identify latent TAND severity trajectories using latent class mixed effect modeling [84]. The number of classes will be chosen based on statistical measures of model fit, the stability of the latent profiles, and the group sizes. Multinomial regression modeling [84] will be used to investigate the association of potential subject-specific covariates with the identified latent classes (predictors of TAND severity trajectories). All analyses will be done using R software (R Foundation for Statistical Computing) [85].

Power calculations are based on the estimation of the time trajectory and comparing different latent trajectories. Based on the data from the preliminary data analyses described earlier of 21 repeat TAND-SQs (42 observations), the power calculations were made in 2 ways. First, based on simulations [86] using a single slope (mean profile), power for sample sizes of n=500 and n=300 was calculated at a slope of -1.05% (power=100%/100%) and at –0.5% (power=97%/81%). Second, simulations were generated for n=500 and n=300 using a 3-trajectory solution with change in trajectories set at +1%, 0%, –1% (power=100%/100%), +0.5%, 0%, –0.5% (power=84%/72%), and 0%, +0.5%, +1% (power=86%/83%). Power calculations allowing for 3 different estimated baseline values of TTSS_max_ (75, 100, and 125) in addition to differing slopes for trajectories, show for n=500, 100% power (with 1% change in trajectories) and 93% power (with 0.5% change in trajectories). A sample size of n=300 using similar power calculations shows 100% power for 1% and 77% power for 0.5% differences in trajectory slopes.

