## Results

### Study Progress

This grant was awarded in December 2023, and funding started in July 2024 (HT94252410790 and HT94252410791). IRB approval was obtained from the University of Cape Town (July 2024), Vrije Universiteit Brussel (November 2024), and the Department of Defense OHRO (December 2024). The TAND Toolkit app was adapted for longitudinal data collection in aims 1 and 2 throughout 2025. Recruitment flyers were cocreated with the TAND consortium and approved by all IRB committees. “Soft launch” for recruitment took place in December 2025, and the official launch of the TAND Toolkit app took place on Rare Disease Day (February 28, 2026). Recruitment will continue until 500 participants are enrolled (anticipated December 2026). Data collection will continue until all participants have completed 5 rounds of data collection (every 3 months over a 12-month period). We anticipate this to continue until December 2027. For aim 3, the experiential and adaptation workshops (objective 3.1) were completed in June 2025, and the pilot intervention (objective 3.2) was delivered in November 2025 with postintervention data collection until May 2026.

Analysis and write-up of aims 1 and 2 will depend on recruitment targets, with primary outputs anticipated by July 2028. Analysis and write-up of aim 3 findings are anticipated by December 2026.

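### Recruitment is said to stop at 500 enrolled, which removes the over-enrolment (up to 600) that the plan relies on against attrition

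*Protocol article*

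**What the plan says.** All places are in the protocol article and concern Aims 1 and 2.

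- **Retention** (Study Participants Aims 1 and 2). The section opens "In light of the risk of attrition in longitudinal research", and its first listed strategy is "inviting more than the target number of participants to enroll (up to 600"). It gives no attrition rate.
- **Study Progress.** "Recruitment will continue until 500 participants are enrolled (anticipated December 2026"). The **Abstract, Results**, says the same: "Recruitment started in December 2025 and will continue until 500 participants are enrolled".
- **Inclusion Criteria.** "A total of 500 adult participants (>18 years of age) will be recruited".
- **Textbox 1, objective 1.2.** Data are to be collected "longitudinally from 500 participants at 5 time points over 12 months".
- **Statistical Analysis Plan (Aim 1).** "power for sample sizes of n=500 and n=300 was calculated" by simulation, and further scenarios follow at the same two sizes. The text does not mention dropout and does not say whether n counts people enrolled or people retained.
- **Potential Challenges and Solutions.** Recruiting and retaining 500 participants is named as the most likely difficulty of the study.

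**The concern.** The plan identifies attrition as a risk and answers it with over-enrolment. That answer works only if enrolment goes past 500. The two statements of when recruitment ends set it at 500 enrolled, so a team that follows them never uses the buffer. Objective 1.2 is then reachable only with no loss at all over 12 months.

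At stake are the Aim 1 power figures for n=500 where the margin is thin, namely the 0.5% per month scenarios. Recruitment is open and expected to close in December 2026. Once it closes at 500, the buffer cannot be recovered.

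**Working it through.** **1. The enrolment statements.** Retention allows up to 600. The Abstract and Study Progress stop at 500 enrolled, and Inclusion Criteria also gives 500. A buffer of 600 for 500 retained corresponds to 1 – 500/600 = 16.7% loss. At that same loss, stopping at 500 leaves 500 × (1 – 0.167) ≈ 417 completers.

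**2. The plan's power figures** (Statistical Analysis Plan, Aim 1), n=500 / n=300:

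| Scenario | n=500 | n=300 |
|---|---|---|
| Single slope –1.05% | 100% | 100% |
| Single slope –0.5% | 97% | 81% |
| +1 / 0 / –1% | 100% | 100% |
| +0.5 / 0 / –0.5% | 84% | 72% |
| 0 / +0.5 / +1% | 86% | 83% |
| Differing baselines, 1% | 100% | 100% |
| Differing baselines, 0.5% | 93% | 77% |

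These cannot be reproduced, because the article does not give the variance components, class shares or test behind the simulations. As a check, I back-solved the noncentrality from each n=500 figure (two-sided 5%; 2 df for three trajectories) and scaled it by n to 300. This gives 84.5% for the single slope at –0.5% (stated 81%), 61% for +0.5/0/–0.5% (stated 72%), 64% for 0/+0.5/+1% (stated 83%) and 74% for differing baselines (stated 77%). Scaling misses the plan's own values for two three-trajectory scenarios, so below I interpolate between the stated figures and show scaling only for the single slope.

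**3. Effective n under attrition.** The following are assumptions, not plan figures: loss of 20%, 30% or 40% by the last visit, spread evenly after visits 1 to 4; visits at months 0, 3, 6, 9 and 12; a random-intercept model that keeps partial data.

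The within-person sum of squares of time for 1 to 5 visits is 0, 4.5, 18, 45 and 90. The relative slope information for loss d is therefore

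(1 – d) + (d/4)(0 + 4.5 + 18 + 45)/90 = 1 – 0.8125d,

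which is 0.838, 0.756 and 0.675, or n ≈ 419, 378 and 338.

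Adding the between-person information needs a residual SD. The 97% figure implies a slope SE of 0.5/(1.960 + 1.881) = 0.130, taking 0.5% as 0.5 units on a baseline near 100. The residual SD is then 0.130 × √(500 × 90) ≈ 27.6. With the baseline SD of 64.2 from the preliminary data, relative information is 0.844, 0.765 and 0.685, so **effective n ≈ 422, 382 and 342**.

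**4. Power at those sizes.** Linear interpolation: P(n) = P(300) + [P(500) – P(300)] × (n – 300)/200, with weights 0.61, 0.41 and 0.21. For example, for +0.5/0/–0.5% at 20% loss: 72 + 12 × 0.61 = 79.3%.

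| Scenario | Stated, n=500 | 20% loss | 30% loss | 40% loss |
|---|---|---|---|---|
| +0.5 / 0 / –0.5% | 84% | 79% | 77% | 75% |
| Single slope –0.5%, interpolated | 97% | 91% | 88% | 84% |
| Single slope –0.5%, scaled | 97% | 94% | 92% | 89% |
| Differing baselines, 0.5% | 93% | 87% | 84% | 80% |
| 0 / +0.5 / +1% | 86% | 85% | 84% | 84% |
| Scenarios near 1% | 100% | about 100% | about 100% | about 100% |

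The scaled row uses Φ(3.841 × √(relative information) – 1.960).

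**5. With 600 enrolled.** The same factors give effective n ≈ 506 at 20% loss and 459 at 30%.

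**6. Aim 2.** With standard errors scaled from the preliminary n=51, the Sobel power at n=300 with halved paths is 86.5%, against the stated 86%. Aim 2 therefore has room for loss.

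**The case against.** **600 may be a number invited, with 500 the target.** The wording is loose enough to allow this. It does not fit the recruitment route, though: flyers and invitations go out through the websites and mailing lists of 38 organizations, one with a database of over 2700 participants, so a cap of 600 invitations would have little meaning. Inviting more people also offsets no attrition if enrolment still ends at 500. What stands is that 600 is a ceiling and not a commitment.

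**The plan already shows n=300.** This has force. 300 is 60% of 500, so it covers complete loss of 40%, and more if partial data count. The figures bracket the shortfall, but the plan does not present them as an attrition allowance, and its own value for +0.5/0/–0.5% at that size is 72%.

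**A condensed article may leave attrition settings to the full plan.** This is fair, and the missing rate is not the point. The point is that two statements in the article give different ends to recruitment.

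**Stronger readings.** A reader might infer that the Aim 1 power as a whole fails. It does not: the scenarios near 1%, which match the preliminary slope of –1.05 units per month, stay at 100% at both sizes. A reader who scales noncentrality might put +0.5/0/–0.5% at 67% for 40% loss. That is below the plan's own 72% at the smaller n=300, so the documents do not support it.

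**Conclusion.** The stated end of recruitment and the attrition buffer conflict, and this rests on the text alone. Under a stop at 500 enrolled, any attrition means that objective 1.2 is not met.

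The loss of power is moderate and confined to the 0.5% per month scenarios. For 20–40% loss with partial data kept, the largest effects are a fall from 84% to about 79–75% for +0.5/0/–0.5%, and from 93% to about 87–80% for differing baselines. These sizes depend on an assumed attrition rate, an assumed dropout pattern, a residual SD inferred from one stated power, and n=500 meaning 500 people with complete follow-up, which the article does not state.

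A reader might also infer that enrolling 600 secures the stated power. That holds at about 20% loss under these assumptions, but not at 30%.

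**What to change.** Choose one of two routes while recruitment is open.

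1. **Use the buffer.** Reword the Abstract (Results), Inclusion Criteria and Study Progress to agree with Retention: recruitment continues past 500, up to the 600 already written, with 500 as the number to be retained. Say in Retention that 600 refers to people enrolled.
2. **Keep 500 enrolled as final.** Remove the over-enrolment statement from Retention. In the Aim 1 analysis plan, state the power for the 0.5% scenarios at the expected retained n, with the n=300 figures as the lower bound.

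Under either route, say whether n in the power statement counts people enrolled or retained, and give the attrition assumed.

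The cost is wording in a few sections. Route 1 asks for nobody beyond the 600 already planned, though recruitment may run past the expected December 2026 close. Route 2 costs a somewhat lower stated power.

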### Study Participants (Aim 3)

#### Inclusion Criteria

For objective 3.1 (adaptation), all members of the TAND consortium, prioritizing those with lived expertise in TSC, will be invited to participate in the adaptation of the “Well-Beans for Caregivers” intervention by participating in 3 experiential sessions of the intervention and an adaptation workshop. All consortium members will be required to sign informed consent prior to participation. Inclusion criteria for objective 3.2 (pilot intervention), potential study participants are (1) adult caregivers (>18 years of age) of a family member with TSC (with any age, sex, genotype, and intellectual level); (2) willingness to provide electronic informed consent; (3) willingness and ability to participate in 3 online intervention sessions (each session will last 2 hours, 1 session per week over 3 weeks); (4) willingness and ability to complete pre-, post-, 3-, and 6-month follow-up data collection; (5) need to have access to a digital device (eg, smartphone, tablet, laptop, or desktop computer) and mobile data or internet access in order to participate in the online intervention sessions; (6) willingness to join a group intervention session; and (7) sufficient level of English to be able to read information, booklets, and participate in sessions and data collection.

#### Recruitment

For objective 3.2 (pilot intervention), 30 participants will be recruited from 3 international sites (10 participants per site). Participants will be recruited via purposive sampling through invitation by our community partners. The invitation email will explain the requirements for participation and include the approved study information form for review. 

#### Enrollment

Participants who wish to participate will be asked to copy their reply to the research team. They will then be sent an email containing a link to the REDCap (Research Electronic Data Capture; Vanderbilt University) platform to sign consent using the e-Consent feature and complete the preintervention forms. They will also receive information about and links to the scheduled intervention sessions.

#### Retention

Due to the brevity of the 3-session intervention and attendance rates in a previous study with this intervention [62], we do not anticipate significant challenges in retention of study participants for aim 3.

### Intervention Delivery

The adapted intervention will be delivered online by 2 trained facilitators (members of the TAND consortium). Trainee facilitators will attend as observers. Sessions will take place once a week for 3 consecutive weeks, in 2-hour sessions, with a group of 10 caregivers. Sessions will follow the manualized script in the adapted facilitator and caregiver booklets. These include stories, exercises, and group discussions to help convey key ACT-informed psychological principles. The content, discussions, and activities cover the main ACT constructs of (1) getting present, (2) identifying personal values, (3) taking small, committed actions in line with these values, (4) finding ways to take care of yourself, (5) naming and noticing your thoughts and feelings, and (6) acceptance, which collectively make up the construct of psychological flexibility [50,81]. This pilot trial has been registered on ClinicalTrials.gov (NCT06879665).

